**Methods:**

A total of 160 postmenopausal women from New Zealand will be recruited and randomized to one of four interventions or treatments for 12 weeks: control, synbiotic supplementation, exercise intervention, or synbiotic supplementation and exercise. The primary outcome measure is the bone and joint biomarkers at baseline and week 12, whereas the gut microbiota profile and inflammatory cytokine measurements will serve as the secondary outcome measures at baseline and week 12. Baseline data and exercise history will be used to assess, allocate, and stratify participants into treatment measures.

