Therefore, modulation with a synbiotic food supplement and weight-bearing low-impact exercise (interventions) can be used to provide data that may contribute to improvements in osteoporotic patient care. This study will use a prospective stratified (by exercise history), randomized, 4-group experimental design with 2 major data collection points (baseline and week 12). Before randomization, participants will be stratified by exercise history (≥2 high-intensity exercise sessions per week and <2 sessions per week) using the International Physical Activity Questionnaire to ensure equal distribution among the 4 groups. However, all participants would be permitted to continue their usual physical activity regime.

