#### Research Questions

What are the effects of dietary interventions with synbiotic food supplements and weight-bearing exercises on bone metabolism, gut microbiota, and micronutrient or inflammation status in postmenopausal women? Do specific gut microbiota alterations moderate bone metabolism? How do individual differences in nutritional interventions affect gut microbiota and, subsequently, bone metabolism? Ultimately, can they be used as a treatment for postmenopausal osteoporosis? Our principal hypothesis is that improvement in bone health, gut microbiota, and inflammation status will be greater in participants randomized to the synbiotic+exercise group compared with participants in the control, synbiotic, or the exercise groups (Figure 1).

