#### Specific Aim

This study aims to examine whether supplementation of fermented milk or dairy (yogurt) with a synbiotic (probiotic+prebiotic) and weight-bearing low-impact exercise could be effective in achieving favorable changes in gut microbiota, inflammation status, and biochemical indexes of bone and joint metabolism.

Aim 1: to compare control, synbiotic, exercise, and synbiotic+exercise groups based on changes in the gut microbiota using 16S rDNA sequencing at baseline and week 12.

Aim 2: to compare control, synbiotic, exercise, and synbiotic+exercise groups based on changes in inflammation status (inflammatory cytokines) at baseline and week 12.

Aim 3: to compare control, synbiotic, exercise, and synbiotic+exercise groups based on changes in bone formation (procollagen type 1 N-terminal propeptide [P1NP]), resorption (cross-linked C-telopeptide of type 1 collagen [CTx-I]), and joint degradation (CTx-II/COMP [cartilage oligomeric matrix protein]) at baseline and week 12.

Aim 4: to compare control, synbiotic, exercise, and synbiotic+exercise groups based on changes in body composition (lean body mass and fat mass), total hip, femoral neck, and spine BMD (DXA [dual-energy x-ray absorptiometry]) at baseline and week 12.

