### Statistical Analyses

G*Power statistical software version 3.1.9.7 developed in Heinrich Heine University Düsseldorf was used to calculate the sample size to ensure 95% CI with an α value of .05. We require 36 participants for each group. The within-subject SD for the primary outcome variables CTx-I and P1NP with a correlation of 0.5 was used. The number of volunteers was increased to 40 to allow for a dropout rate of 10%.

The results will be presented as either percentages or mean differences. Normality tests will be assessed through Shapiro-Wilk tests carried out on each parameter before analysis. The conventional analysis of variance (ANOVA) for RCT analysis will be used, and ANOVA for repeated measures will be applied to study treatment differences, period effect, and the interaction between treatment and period (carryover effect). IBM SPSS version 25 and Minitab statistical software version 19 (Minitab LLC) will be used for statistical analyses. Comparing groups' pretest with Mann–Whitney U test and then comparing pre- and postintervention results with Wilcoxon is one option and transforming data into ranks and performing an analysis of covariance (or ANOVA) is another option. All analyses will be considered statistically significant at *P*≤.05.

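### The repeated-measures ANOVA labels treatment-by-period as carryover, although in this two-visit parallel trial that term is the between-arm difference in change that the aims target

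*Protocol article*

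**What the plan says.** On design, the abstract's Methods paragraph has participants "randomized to one of four interventions or treatments for 12 weeks", and the Overview describes a "randomized, 4-group experimental design with 2 major data collection points (baseline and week 12"). No switch of treatment, sequence or washout appears anywhere.

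On objectives, Specific Aim compares the four arms on changes between the two visits; Aim 3, for instance, compares "groups based on changes in bone formation" and the other bone and joint markers. The principal hypothesis under Research Questions is that improvement in bone health, gut microbiota and "inflammation status will be greater in participants randomized to the synbiotic+exercise group" than in the other three arms.

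On analysis, the Statistical Analyses section first says that "The conventional analysis of variance (ANOVA) for RCT analysis will be used", without giving the dependent variable. The same sentence adds that "ANOVA for repeated measures will be applied to study treatment differences, period effect, and the interaction between treatment and period (carryover effect"). Analysis of covariance appears only on ranks, as one of two options, with ANOVA as its alternative.

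**The concern.** In a crossover trial, participants pass through several treatment periods, and a treatment-by-period interaction can signal carryover, a nuisance that casts doubt on the treatment comparison. Here each woman has one treatment, and 'period' can only mean baseline versus week 12. The interaction is then the difference between arms in change, which is the effect the aims and the principal hypothesis describe. The plan gives the contrast that answers its questions the name of a nuisance effect.

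Two things are at stake. A real treatment effect could be reported as carryover and treated as a flaw. And an analyst looking for efficacy in that model could turn to the other listed item, treatment differences. As a main effect, it averages a pre-treatment measurement with the week-12 measurement and so dilutes the effect.

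**Working it through.** **The plan's own figures.** 36 / (1 − 0.10) = 40 per group, and 4 × 40 = 160. This reproduces. The 36 itself can be neither reproduced nor refuted, because the article gives no effect size, SD value or power. The present point does not touch the sample-size figures.

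**Inputs.**
- Two visits, four parallel arms, 36 evaluable per arm, alpha .05 (protocol article). Two-sided testing is assumed.
- Pre-post correlation ρ = 0.5. This is an assumption. The article says "The within-subject SD for the primary outcome variables CTx-I and P1NP with a correlation of 0.5 was used", which does not say what is correlated with what, so a range of 0.3 to 0.8 is shown.
- Effect size: assumed, chosen so that the pairwise treatment-by-time contrast has 80% power at 36 per arm.
- Equal SD s at both visits, and no baseline difference between arms, as expected under randomization. The true week-12 difference is D.

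**What each term estimates, for two arms.**

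| Analysis | Expected difference | Variance per woman | At ρ = 0.5 |
|---|---|---|---|
| Treatment main effect (mean of the two visits) | (0 + D)/2 = D/2 | s²(1 + ρ)/2 | 0.75 s² |
| Treatment-by-time (change) | D − 0 = D | 2s²(1 − ρ) | 1.00 s² |
| ANCOVA of week 12 on baseline | D | s²(1 − ρ²) | 0.75 s² |

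The halving in the first row holds for any ρ.

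**Signal per unit of D/s at ρ = 0.5.** Main effect 0.5/√0.75 = 0.577; interaction 1/√1 = 1.000; ANCOVA 1/√0.75 = 1.155. The main effect therefore needs (1.000/0.577)² = 3.0 times the n of the interaction and (1.155/0.577)² = 4.0 times that of ANCOVA.

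**Power at 36 per arm, ρ = 0.5.** For 80% power on the interaction, D/s = (1.960 + 0.842) × √(2/36) × 1.000 = 0.660 by the normal approximation, or 0.670 with the t distribution.
- Main effect: 0.660 × 0.577 × √(36/2) = 1.617, and Φ(1.617 − 1.960) = 36.6%. For 80% power it needs 3 × 36 = 108 per arm (107 with t).
- Interaction: 80%, by construction.
- ANCOVA: 0.660 × 1.155 × √(36/2) = 3.234, and Φ(3.234 − 1.960) = 89.9%. For 80% power it needs 0.75 × 36 = 27 per arm (28 with t).

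**Range over ρ, with the interaction held at 80% power.**

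| ρ | D/s | Main-effect power | ANCOVA power | n ratio, main effect to interaction |
|---|---|---|---|---|
| 0.3 | 0.781 | 54% | 93.5% | 1.86 |
| 0.5 | 0.660 | 37% | 89.9% | 3.00 |
| 0.7 | 0.511 | 22% | 86.0% | 5.67 |
| 0.8 | 0.418 | 15% | 84.0% | 9.00 |

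**Four-arm check by simulation** (10,000 runs, 36 per arm, ρ = 0.5, an effect of 0.66 SD in the combination arm only). Omnibus power was 34% for the main effect, 82% for the interaction and 92% for ANCOVA. Under the null, all three rejected in just under 5% of runs, so type I error is not inflated.

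**The case against.** The strongest reply is that only a label is wrong. Treatment-by-period is in the planned model, so the correct contrast will be fitted, and Specific Aim states that change is what is compared. A reader might infer from the sentence that efficacy will be judged on the treatment main effect, because treatment differences are listed apart from an interaction assigned to carryover. The article does not say so: it lists three items to be studied and makes none decisive. The claim that the trial's efficacy conclusion rests on a halved contrast therefore goes beyond the text.

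The separately named conventional ANOVA also matters. Run on change scores, it would be identical to the treatment-by-time test. But its dependent variable is not stated and nothing ranks it above the repeated-measures model, so it neither proves the stronger reading nor resolves the ambiguity.

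Two further objections stand. The power figures depend on an effect size the article does not give and on one reading of the 0.5. And analysis of change is valid in a randomized trial, so not making ANCOVA primary is a loss of efficiency, not an error.

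What does not stand is the idea that the label is harmless. It tells the analyst how to interpret the F test that answers Aims 1 to 4, and that interpretation is wrong for this design. A fuller analysis plan may add detail, but the sentence as published is a misstatement, not an omission.

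**Conclusion.** The point holds for the repeated-measures ANOVA. It is certain from the text that crossover terms are applied to a parallel trial with two visits, that carryover cannot occur, and that the term so labelled is the between-arm difference in change.

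The consequence is conditional. If efficacy were read from the treatment main effect, the estimate would be half the week-12 effect, given only no baseline difference. The loss of power is illustrative: about 37% against 80% at an assumed pre-post correlation of 0.5 and an assumed effect of about 0.67 SD, and between 54% and 15% for correlations from 0.3 to 0.8. The documents do not establish that the sponsor will read the main effect in this way. The harm would be dilution, lost power and misinterpretation, not false-positive findings.

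**What to change.** In the Statistical Analyses section:

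- Delete the period and carryover wording.
- State as the primary efficacy analysis the between-arm difference at week 12 from ANCOVA, adjusted for the baseline value and the exercise-history stratum described in the Overview. Report adjusted differences with 95% CIs. The baseline adjustment is recommended as an efficiency gain: at a correlation of 0.5 the residual variance is 0.75 s² against 1.00 s² for change scores.
- If repeated-measures ANOVA is kept, name treatment-by-time as the treatment effect and do not interpret the treatment main effect.
- Leave any transformation to the distribution checks already planned; nothing in the article fixes a scale.

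The cost is the rewording of one paragraph. Baseline values and exercise history are already collected, the sample size does not change, and the named software can run the analysis.

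### The repeated-measures ANOVA labels the treatment-by-period interaction as carryover, but in this parallel trial that term is the between-arm difference in change and should not be treated as a nuisance

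*Protocol article*

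**What the plan says.** The Methods part of the Abstract says that the women "will be recruited and randomized to one of four interventions or treatments for 12 weeks". The Overview describes a "randomized, 4-group experimental design with 2 major data collection points (baseline and week 12"). No section describes a second treatment period, a treatment sequence or a washout.

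In Specific Aim, all four aims compare the groups on change. Aim 3, which covers the bone and joint markers, is "to compare control, synbiotic, exercise, and synbiotic+exercise groups based on changes in bone formation" and the other markers at baseline and week 12.

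The Statistical Analyses section opens its model statement with "The conventional analysis of variance (ANOVA) for RCT analysis will be used" and continues, in the same sentence, that "ANOVA for repeated measures will be applied to study treatment differences, period effect, and the interaction between treatment and period (carryover effect"). It then lists rank-based alternatives as options: Mann–Whitney on the pretest with pre/post Wilcoxon, or ANCOVA or ANOVA on ranks. It does not say which of these analyses decides the primary outcome.

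**The concern.** Treatment, period and a treatment-by-period term read as carryover are the components of a two-period crossover analysis. Here the two periods are the two visits, one before treatment and one after it. With two visits, the treatment-by-period interaction is the between-arm difference in change, so the term that answers the aims carries the name of a nuisance effect. The term whose name suggests efficacy is the treatment main effect, which averages a visit at which the arms cannot truly differ with the visit at which they may.

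This is a wrong statement about what a model term means, so it is not a detail that a condensed article leaves to a fuller document. At stake is how the results for CTx-I and P1NP are described. An analyst who follows the labels could report a genuine effect as carryover and give a half-size, weakly powered quantity as the treatment difference.

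**Working it through.** **Inputs from the article.** Four arms with one 12-week assignment each; visits at baseline and week 12; 36 evaluable women per arm; α = .05; a correlation of 0.5. **Assumptions.** The 0.5 is the correlation r between baseline and week 12 (the article does not say what it correlates); equal variance σ² at both visits; two-sided tests; complete data; 80% reference power (the article states no power or effect size).

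**The plan's own figure.** 36/(1 − 0.10) = 40 per arm, and 4 × 40 = 160, so the dropout step reproduces. The 36 cannot be re-derived, because the effect size, SD and power are not printed. No claim is made here about it.

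**What each term estimates.** Let δ be the week-12 difference between two arms. Randomization makes the expected baseline difference 0.
- Interaction (difference in change): δ − 0 = δ. Per-woman variance: 2σ²(1 − r).
- Treatment main effect (mean of both visits): (0 + δ)/2 = δ/2. Per-woman variance: σ²(1 + r)/2.

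The halving holds for any r and σ.

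**Relative information.** The ratio of noncentralities, main effect to interaction, is [0.25/((1 + r)/2)] / [1/(2(1 − r))] = (1 − r)/(1 + r). At r = 0.5 this is 0.5/1.5 = 0.333.

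**Pairwise power (1 df), r = 0.5, σ = 1.** The SD of change is √(2 × 0.5) = 1. For 80% power, δ = (1.960 + 0.842) × 1 × √(2/36) = 0.660. For the main effect the SD is √0.75 = 0.866, so its standardized signal is 0.330/(0.866 × 0.2357) = 1.617. Power is Φ(1.617 − 1.960) = 36.6%.

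**Four-arm F test (3 and 140 df).** 80% power needs noncentrality 11.21. One third of that, 3.74, gives 32.8%.

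**Range over r**, with the interaction held at 80%:

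| r | noncentrality ratio | main effect, 3 df | main effect, 1 df |
|---|---|---|---|
| 0.3 | 0.54 | 51% | 54% |
| 0.5 | 0.33 | 33% | 37% |
| 0.7 | 0.18 | 19% | 22% |

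With 90% as the reference and r = 0.5, the figures are 41.8% (3 df) and 46.5% (1 df).

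**Simulation check.** With one arm shifted by 0.8 SD at week 12, 36 per arm and r = 0.5, the interaction was significant in 94.6% of runs and the main effect in 49.1%.

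**Baseline-adjusted comparison.** The residual variance is σ²(1 − r²) = 0.75 at r = 0.5, against 1.0 for change. The same δ gives 0.660/(0.866 × 0.2357) = 3.235, and power is Φ(3.235 − 1.960) = 89.9%.

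**The case against.** The strongest reply is that the harm is inferred. A reader might conclude that efficacy will be read from the diluted main effect, so that the trial is bound to lose more than half its power. The article does not support that. It never uses the term main effect, never makes that term the efficacy test, and never says that the interaction will be set aside. It lists the interaction among the things to be studied, and the aims state the comparison correctly as one of changes.

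The same sentence also plans a conventional ANOVA. At r = 0.5, week-12 values and changes have the same variance, because 2(1 − 0.5) = 1. A conventional ANOVA on either response would therefore match the interaction's power. Rank ANCOVA is listed too.

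These points limit the finding but do not remove it. The conventional ANOVA has no named response variable and is not made primary, and the rank methods are only options. The repeated-measures model is the only analysis whose terms are spelled out, and one of them is given a meaning that it cannot have in this design.

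Two further inferences should be avoided. The existence of several possible tests raises a separate multiplicity question. It cannot be added to the power loss, which arises only if the main effect alone is read. Nor is chance baseline imbalance a reason to prefer the interaction. Given an observed imbalance b, the main effect is expected to carry (1 + r)/2 × b = 0.75b at r = 0.5, and the difference in change carries −(1 − r)b = −0.5b.

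**Conclusion.** The carryover label is wrong for this design and contradicts the article's own description of a parallel trial with change-based aims. The term so labelled is the treatment effect that the aims ask for, and the term listed as treatment differences estimates half of the week-12 effect. That much follows from the design alone.

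The possible loss of power, from an assumed 80% to about 33% (3 df) or 37% (1 df), is conditional. It needs the labels to be followed, 36 evaluable women per arm, and the stated 0.5 to be the baseline to week-12 correlation. Over r = 0.3 to 0.7 the main-effect power lies between about 54% and 19%. The article makes this misreading possible but does not commit the trial to it.

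**What to change.** Delete the words on carryover and the period terminology from the Statistical Analyses section, and name one efficacy test.

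- **Preferred:** the between-arm comparison of week-12 values adjusted for baseline (ANCOVA). It is a different test from the treatment-by-time term and is more powerful: about 90% where the change analysis has 80%, at r = 0.5.
- **Otherwise:** the treatment-by-time interaction, described as the between-arm difference in change from baseline to week 12.

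State that the treatment main effect over both visits and the period (time) effect are not evidence of efficacy. Choose one of the two tests before the data are seen, and do not leave both open.

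The cost is a few sentences in the protocol or analysis plan. No new data, visits or participants are needed.

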## Methods

### Participants

The G*Power statistical software, version 3.1.9.7, developed in Heinrich Heine University Düsseldorf, was used to calculate the sample size using the bone biomarker CTx-I; a recommended number of 36 women would be required for the study. However, 40 women aged >60 years will be recruited for each of the 4 groups to allow for a possible dropout rate of 10%. The test groups will receive the synbiotic food supplementation and exercise program (10,000 steps brisk walking per day required), whereas the control group will receive a placebo and no exercise; however, dietary intake and exercise will be monitored by a 3-day diet diary and the International Physical Activity Questionnaire. All study participants will read the information sheet, and signed and written consent forms will be obtained from them.

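### One of the two alternative analyses listed beside the ANOVA has no between-arm test of outcome, and no rule says which alternative applies

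*Protocol article*

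**What the plan says.** All the relevant analysis text is in the second paragraph of Statistical Analyses in the protocol article.

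- **Normality check.** "Normality tests will be assessed through Shapiro-Wilk tests carried out on each parameter before analysis".
- **Main analysis.** Conventional ANOVA, and repeated-measures ANOVA with treatment, period and their interaction. The interaction is a between-arm test of change.
- **Alternatives.** One sentence gives two. The first is a Mann-Whitney test of the groups' pretest values followed by a Wilcoxon test. The second is a rank transformation followed by ANCOVA or ANOVA. The sentence runs: "and then comparing pre- and postintervention results with Wilcoxon is one option and transforming data into ranks". The article does not say when an alternative replaces the ANOVA, or which of the two would be used.

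The trial's questions concern differences between arms. Under Research Questions, the principal hypothesis is that the combination arm improves more than each of the other three. Under Specific Aim, all four aims have the same form, for example "to compare control, synbiotic, exercise, and synbiotic+exercise groups based on changes in inflammation status".

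**The concern.** The first alternative does not contain the comparison that the trial is designed to make. Its Mann-Whitney step looks only at values before treatment, where randomised groups differ by chance. It is also a two-sample test, while four arms give 4 × 3 / 2 = 6 pairs, and the article does not say which pair is meant. Its Wilcoxon step sets week 12 against baseline. Whether that is done within each arm or on pooled data is not stated, but neither way tests one arm against another.

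The conclusion would then have to rest on a pattern such as a significant fall in an active arm and none in control, which is not a test of the difference between them. Any change common to all arms, for example from taking part, from placebo or from assay drift, would be credited to treatment. No outcome is exempt, so this route is open for the primary markers CTx-I and P1NP. The two alternatives can also disagree on the same data, and the text as written allows the choice to be made after the results are seen.

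**Working it through.** **Inputs from the article (Participants; Statistical Analyses)**

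- Arms: "40 women aged >60 years will be recruited for each of the 4 groups".
- Evaluable number: "We require 36 participants for each group".
- Significance level: 0.05 ("to ensure 95% CI with an α value of .05"). Sidedness is not stated; two-sided is assumed.
- Correlation: "The within-subject SD for the primary outcome variables CTx-I and P1NP with a correlation of 0.5 was used". It is taken here as the pre-post correlation.

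**The plan's own figure.** With 10% dropout, 36 / (1 − 0.10) = 40 per group, as stated. The 36 itself cannot be re-derived, because no effect size, SD value or power is given. The article states no error rate for the alternative analyses.

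**Assumptions not in the article.** The marker is lognormal. There is no difference between arms. A common favourable shift, control included, is expressed in baseline SDs on the log scale.

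**Simulation.** Four arms of 36 and 2,000 trials per setting. The Wilcoxon signed-rank test is run in each arm, and an arm counts as improved if p ≤ 0.05 and the median change is favourable. On the same data, rank ANCOVA tests all four arms together, with baseline rank as covariate. Monte Carlo error is about 2 percentage points at most.

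| Common shift (SD) | One given active arm improves | At least one active arm improves | At least one active arm improves, control not significant | Rank ANCOVA significant |
|---|---|---|---|---|
| 0 | 2.8% | 7.6% | 7.1% | 4.3% |
| 0.1 | 8.1% | 21.2% | 19.6% | 5.1% |
| 0.2 | 21.2% | 48.3% | 39.4% | 5.7% |
| 0.3 | 36.7% | 74.8% | 46.5% | 5.1% |
| 0.4 | 59.3% | 93.5% | 38.9% | 4.7% |
| 0.5 | 77.7% | 99.1% | 20.3% | 5.4% |

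**Closed-form checks** (the arms are independent)

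- No shift, improvement only: 1 − 0.975³ = 7.3% for at least one of three active arms. Multiplying by 0.95 for a non-significant control gives 6.9%, against 7.1% simulated.
- No shift, change in either direction: 1 − 0.95³ = 14.3%, against 13.9% simulated.
- Shift of 0.3 SD: with p = 0.367 in every arm, (1 − p) × [1 − (1 − p)³] = 0.633 × (1 − 0.254) = 47.2%, against 46.5% simulated.

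The discordant pattern falls again beyond 0.3 SD because control then becomes significant too. The within-arm tests themselves keep getting worse: at 0.5 SD an active arm appears to improve in 99% of trials with no treatment effect.

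**The case against.** The strongest reply is that the plan does compare the arms. The ANOVA and repeated-measures ANOVA are stated as what will be done, and the Wilcoxon route is only one option. The same sentence offers rank ANCOVA or ANOVA, which is a between-arm analysis; rank ANCOVA held 4.3% to 5.7% at every shift tried. This stands. A reader might infer that the plan, or its whole non-parametric fallback, never compares the arms. The article does not support that.

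Three further points also stand.

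- **The trigger is inferred.** The article does not say that the alternatives apply when Shapiro-Wilk rejects. It gives no distribution or coefficient of variation for any marker, so how often they would be used cannot be estimated from it.
- **The high rates are conditional.** With no shared shift, one arm stays near its nominal level (2.8% for improvement), and the excess comes from testing three active arms. The 13.9% for any significant change includes worsening, so it is not a rate of claimed benefit. Nor is regression to the mean an evident source of shift, since the eligibility criteria do not select on the bone turnover markers or cytokines.
- **An analysis plan may settle the choice.** Selecting and ordering methods is commonly left to that document, which is not shown.

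None of this rescues the Wilcoxon route. The article itself lists a method that cannot answer its hypothesis and puts it on a level with one that can. That is a wrong entry, not a detail left for later.

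**Conclusion.** The point holds for one of two unranked alternatives, not for the analysis as a whole. The Mann-Whitney and Wilcoxon route contains no between-arm test of outcome and cannot test the principal hypothesis or the four aims. That conclusion follows from the text and needs no assumption.

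The size is illustrative. With no true difference between arms, an active arm improves significantly while control does not in about 7% of trials without a shared shift, 20% at 0.1 SD, 39% at 0.2 SD and 47% at 0.3 SD. This rests on per-arm Wilcoxon tests, a two-sided 5% level, a correlation of 0.5, an assumed lognormal marker and assumed shift sizes. Some shared change is plausible, since controls take placebo and have diet and activity monitored, but the article gives no size for it. A reader might take 47% as the false-positive rate of this trial. It is not: it applies only if this route is used and a shift of that size occurs. The rank ANCOVA column is an overall four-arm test, so it shows that the 5% level is held and is not a like-for-like count of the same pattern.

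**What to change.** In Statistical Analyses:

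1. Delete the Wilcoxon pre-post option and the Mann-Whitney tests of baseline.
2. Name one baseline-adjusted between-arm analysis as the alternative to the ANOVA: the rank ANCOVA already listed. ANCOVA on the log scale is equally acceptable if prespecified, but log transformation is not needed to cure this defect.
3. State when the alternative is used, so that the choice does not depend on the results.

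The cost is wording only. Sample size, visits and data collection are unchanged.
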